### Design

There will be 3 treatment sessions and an additional training program for 6 weeks. Follow-up assessments will take place after 6 weeks, 3 months and 6 months. The 3 treatment session will always be 4 days apart. At baseline the participant will fill out the Visual Analogue Pain Rating Scale (VAS), the Neck Disability Index (NDI) and the European Quality of Life 5 Dimensions 5 Levels (EQ-5D-5 L) [38–45]. At two subsequent treatment sessions, the patient will be asked to fill out the NDI, VAS, EQ-5D-5 L, and the Patients Global Impression of Change Scale (PGIC) before the treatment [46]. The VAS will be repeated after each treatment. For the follow-up assessments the participants will receive the same questionnaires (Fig. 2).

**Fig. 2 Fig2:**
[figure not shown]
Flowchart of the trial. Flowchart of the trial showing how the participants were allocated to the different groups and the follow-up

### History taking and physical examination

Baseline measurements as stated above, will be followed by a history taking and physical examination (P/E). History taking includes questions referring to the onset, episode, nature and location, as well as factors that increase or decrease the pain, medication use, occupation, sick leave and other treatments that have already been tried. The P/E will start with a neurological screening (motor, reflex and sensory testing) followed by Spurling’s test, cervical distraction test and neurodynamic upper limb test [47–50]. These evaluations are added to confirm that the patient is eligible to participate in the study. If one of the previous tests is positive the patient will be excluded from the study at this point. Next the segmental mobility of the entire thoracic spine will be tested. In this study a dysfunctional segment is defined as a painful segment, that is produced using prone springing palpation for pain provocation [51, 52]. We define the painful segment as the treatment segment [53]. The testing and marking of the thoracic spine will be carried out by an orthopedic manual therapy (OMT)-trained physical therapist, who will also be applying the manipulations. The most painful segment is marked with a waterproof marker and then photographed; followed by the randomized treatment of the painful thoracic segment. Other painful and/or hypomobile segments will be marked and reported but they will not be treated.

### Randomization

A clinician, who is not involved in the study, will independently conduct the randomization procedure. A block randomization (20 blocks of 4) using a computer-based randomization program will be conducted. The original randomization list will be stored in an opaque and sealed envelope not accessible to the therapist conducting the manipulations. Eighty sequentially numbered, sealed, opaque envelopes, containing the randomized group allocation will be prepared. At the time of treatment, these envelopes will be given to the therapist applying the manipulation, immediately prior to the execution of the manipulation. The patient will be unaware of the technique that will be applied, only that the technique may either be delivered manually or with an electromechanical instrument (Impulse iQ®, Neuromechanical Innovations, Chandler, AZ, USA). To minimize any possible effects of expectations of treatment, each participant will be asked prior to the first treatment about their expectations regarding new and conventional treatments.

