### Blinding

To minimize performance bias, the therapist who is conducting the treatment will be kept unaware of the treatment method until the manipulation is applied. Additionally, the questionnaires that are filled out by the patient are put inside sealed, opaque envelopes. The therapist is unaware of the patient-assessed outcome. When data is entered into the database the researcher will be unaware of the associated participant due to de-personalization/anonymity of the questionnaires.

Additionally, the expectations of the patient regarding the new and conventional treatments are retrieved beforehand and taken into consideration during the evaluation of the data.

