### Statistical methods

#### Number of test subjects

The sample size was calculated with the formula:$$ \mathrm{n} = \mathrm{f}\left(\upalpha, \upbeta /2\right)*2*{\upalpha}^2/{\mathrm{d}}^2 $$

Therefore: 2 × [(1.96 + 0.842)^2^ × 15^2^]/12^2^ = 24.53 [60]

The significance level alpha was chosen at 5 % and the power of 80 %.

From the literature, an expected standard deviation of 15 mm of a VAS can be determined [19]. For the expected mean difference the minimal clinically significant difference (12 mm) on the VAS was determined [61]. To be able to accomplish all needed participants, 2 patients per group will be added addressing possible withdrawals, missing data, and losses to follow up [62]. Therefore, a total of 54 patients will be recruited (27 per arm).

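### A fixed, disclosed block size of 4 makes up to about 32% of allocations predictable to a single treating therapist, so concealment is partly compromised

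*Protocol article*

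**What the plan says.** The Randomization section fixes the scheme: "A block randomization (20 blocks of 4) using a computer-based randomization program will be conducted". It continues: "Eighty sequentially numbered, sealed, opaque envelopes, containing the randomized group allocation will be prepared". No strata and no varying block sizes are described. The list itself is kept from the therapist, but of the envelopes the section says that "these envelopes will be given to the therapist applying the manipulation, immediately prior to the execution of the manipulation".

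Under History taking and physical examination, the testing and marking of the thoracic spine are "carried out by an orthopedic manual therapy (OMT)-trained physical therapist, who will also be applying the manipulations". This takes place at the visit where screening tests can still remove a patient: "If one of the previous tests is positive the patient will be excluded from the study at this point". The treated segment is the most painful one on springing palpation. It is marked and photographed before the randomized treatment.

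The Blinding section says that "the therapist who is conducting the treatment will be kept unaware of the treatment method until the manipulation is applied". The Discussion repeats this as a response to the trial's weakness on blinding, and relies on independent randomization and sealed envelopes to limit selection bias. The Trial status section says that recruitment is ongoing.

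**The concern.** A sealed envelope hides one allocation. It does not hide a sequence whose remaining entries can be deduced. The two techniques are unmistakable to the person delivering them: one is a manual thrust with the patient supine, the other a device applied with the patient prone. The therapist therefore accumulates the list as it is used, and the envelope numbers show the position within each block. Once the block size is known, the end of many blocks is known too.

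What is at stake is the period before the envelope is opened. In that period the therapist judges which segment is most painful, and the patient can still be excluded. Foreknowledge of the arm could colour those judgements, which is what concealment is meant to prevent. The Blinding statement would then be untrue for the predictable patients.

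**Working it through.** **Inputs.** Block size 4, 20 blocks and 80 envelopes (Randomization). Total 54, 27 per arm (Number of test subjects), hence 1:1 allocation and two of each arm per block. The therapist opens the envelope and delivers the treatment (Randomization; History taking and physical examination). Assumed: the therapist knows the block size and remembers earlier allocations in the block.

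**The plan's own figures.** 2 × (1.96 + 0.842)² × 15² / 12² = 24.53, rounded up to 25; 25 + 2 = 27 per arm; 2 × 27 = 54. The list is 20 × 4 = 80. Both reproduce, and neither is affected by this point.

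**Known with certainty, one therapist.** An allocation is certain when one arm is already used up in its block. There are six equally likely orders of two and two.

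- Positions 1 and 2: never certain.
- Position 3: certain if the first two match, probability 1/3.
- Position 4: always certain.

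Expected per block: 1/3 + 1 = 4/3, or 33.3% of a complete block. Fifty-four patients make 13 complete blocks plus 2 patients, and those last 2 are never certain. So 13 × 4/3 = 17.3, and 17.3 / 54 = 32.1%.

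**Best guess, one therapist.** Chances of a correct guess by position are 1/2, 2/3, 2/3 and 1. The sum is 2.83, and 2.83 / 4 = 70.8% per complete block, against 50% with no foresight. Over 54 patients: (13 × 2.833 + 1/2 + 2/3) / 54 = 38.0 / 54 = 70.4%.

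**Several therapists.** Suppose k therapists share one list, patients fall to them at random and they exchange no information. A certain prediction then also needs both earlier patients of the used-up arm to have been treated by the therapist now making the prediction, which has probability 1/k². The share in complete blocks becomes 1/(3k²).

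| Therapists | Share known with certainty |
|---|---|
| 1 | 1/3 = 33.3% (32.1% over 54 patients) |
| 2 | 1/12 = 8.3% |
| 3 | 1/27 = 3.7% |

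A simulation of 100,000 blocks gave 33.4%, 8.2% and 3.7%.

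**Varying block sizes.** These figures come from simulating 54 patients 3,000 times, with one therapist who knows the set of sizes but not their order.

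| Block sizes | Certain, of 54 | Share | Best guess correct |
|---|---|---|---|
| 4 only | 17.3 | 32.0% | 70.3% |
| 4, 6 | 3.0 | 5.6% | 69.0% |
| 2, 4, 6 | 2.2 | 4.0% | 70.1% |
| 4, 6, 8 | 1.3 | 2.4% | 67.8% |

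Varying the sizes removes most certain knowledge. It hardly changes the success of an informed guess.

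**The case against.** The strongest objection is that the article never gives the number of therapists. The singular may describe a role, and with two or three who share nothing the problem shrinks to about 8% or 4%. That stands, and the 32% must be read as an upper figure tied to one therapist.

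The route to selection bias is also narrow. Practice clinicians recruit and obtain consent, a research assistant verifies the criteria, and neither is said to see allocations. Exclusion at the examination follows a stated rule. The article names the treating therapist for the thoracic testing and marking, not for the neurological screening. The segment is chosen by a rule and photographed. All this limits the harm, but finding the most painful segment by palpation remains the therapist's judgement, made when the arm may already be known.

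A reader might infer more than the documents support:

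- That allocation is not concealed at all. About two thirds of allocations remain uncertain even to a single therapist, and nothing shows that anyone predicted the rest.
- That 80 envelopes contradict 54 patients. The surplus is spare capacity. A last block left incomplete could shift the arms to 28 and 26, which is of no consequence.
- That block size causes performance bias once the envelope is open. Therapist and patient see the technique under any randomization scheme.

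**Conclusion.** The point holds in a limited form. With one therapist who treats everyone and knows the block size, about 17 of 54 allocations (32%) can be known with certainty in advance. The Blinding statement therefore cannot be relied on for those patients. The figure rests on the single-therapist reading and on knowledge of the block size, which the article itself made available during recruitment. It measures what could be foreseen, not what was. The sample size is untouched. This is a weakness worth correcting because the remedy is cheap. It does not invalidate the randomization.

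**What to change.** The independent clinician should regenerate the envelopes not yet opened, using randomly varying block sizes (for example 2, 4 and 6). Neither the sizes nor their order should be disclosed to the therapist or the recruiters. For the patients still to be randomized, certain knowledge then falls to about 4%, or less if the set of sizes is also unknown. Best-guess success stays near 70%, so the change should not be presented as making the sequence unpredictable.

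The number of treating therapists should be stated, since the size of the problem depends on it. If too few patients remain for new envelopes to help, the fixed block size should be reported as a limitation, and the statements in the Blinding section and the Discussion qualified.

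The cost is one new list and set of envelopes from the same person, and a possible imbalance of a patient or two between the arms. A separate sign-off of eligibility and segment would add little: the protocol already places those steps before the envelope, and a predicted arm is known before it arrives.

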### Blinding

To minimize performance bias, the therapist who is conducting the treatment will be kept unaware of the treatment method until the manipulation is applied. Additionally, the questionnaires that are filled out by the patient are put inside sealed, opaque envelopes. The therapist is unaware of the patient-assessed outcome. When data is entered into the database the researcher will be unaware of the associated participant due to de-personalization/anonymity of the questionnaires.

Additionally, the expectations of the patient regarding the new and conventional treatments are retrieved beforehand and taken into consideration during the evaluation of the data.

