### Mechanical

For the Impulse iQ® (Neuromechanical Innovations, Chandler, AZ, USA) the patient lies prone on a treatment table, with arms next to the body, in a relaxed position. Before the treatment begins, the patient is instructed that they will hear a rattling sound that indicates the thrusts conducted by the device and a beep at the end of the treatment. The Impulse iQ® (Neuromechanical Innovations, Chandler, AZ, USA) is then put onto the vertebra that has been identified as a painful segment. A double stylus and middle force setting (peak force = 200 N), as recommended by the manufacturer for the treatment of the thoracic spine, will be used [54]. The device records and analyzes the spinal acceleration response each time a thrust is delivered using the built-in firmware. The machine then produces a series of repetitive thrusts monitoring the acceleration response and, if the response is improving, treatment continuous up to 3 s. If the acceleration response is negative (flat line or decrease) the thrust delivered by the instrument ceases (Figs. 5 and 6).

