### Statistical analyzes

Descriptive statistics will be used to illustrate the empirical data and research population. The Shapiro-Wilk test will be used to assess whether all the variables are normally distributed. If the data is normally distributed the changes of VAS will be analyzed using analysis of variance (ANOVA) (repeated measures) to explore possible significant interaction (group x time) effects (α[1]0.05). Secondary outcome variables will be compared using the Wilcoxon test for matched pairs including confidence intervals. Participants will be sub-grouped into acute and chronic to compare the outcomes. To analyze the outcome of the PGIC, patients will be split into 2 groups (dichotomized): improved (6 and 7) and not improved (1 to 5). With the help of logistic regression, the predicted probability of the outcome will be assessed using the PGIC as dependent variables (improved/not improved). Independent variables will be age, sex, expectations, manipulation and duration of complaints. Missing data will be analyzed using an intention-to-treat method. The data will be collected, stored and analyzed in the IBM-SPSS 22 (PASW, Chicago, IL, USA) statistics program.

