## Discussion

The purpose of this study is to compare treatment outcomes for neck pain patients using manual versus instrument-assisted mechanical manipulation at the thoracic spine. For this aim, a randomized clinical trial is the appropriate study. There are already existing trials and reviews that have investigated the treatment of the thoracic spine in neck pain patients [20, 24–30]. Although there are trials that have compared mechanical and manual manipulations [34, 35], no study has worked with the Impulse iQ® (Neuromechanical Innovations, Chandler, AZ, USA). There are several factors which will support the outcome of the study. These are based on the latest knowledge about the treatment of neck pain. First, patients will receive a treatment using an interval of 4 days between each manipulation. This is recommended in the clinical prediction guideline rules for the use of thoracic manipulations in neck pain patients. Second, we added a home exercise program. It is recommended to combine manipulations of the spine with exercises, to have the strongest benefit for patients with neck pain [8]. Third, all outcome measures that are used (VAS, NDI, EQ-5D-5 L) are valid and reliable and have been often used in research. Fourth, to minimize selection bias, a person not involved in the study conducted the randomization of the participants using a computer program. The outcome of the data sheet was then written on cards and put inside opaque, sequentially numbered and sealed envelopes.

One of the trial’s weaknesses might be regarding blinding. We addressed this issue in different ways. To minimize performance bias, the therapist who is conducting the treatment will be unaware of the treatment method until the manipulation is applied. Additionally, the filled-in questionnaires are put inside a sealed, opaque envelop by the patient. The therapist is unaware of the outcome. When the data is put into the database the therapist will be unaware of the associated participant due to de-personalization/anonymity of the questionnaires. Additionally, the expectations of the patient regarding the new and conventional treatment are retrieved beforehand and taken into consideration during the evaluation of the data.

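### The primary VAS model adjusts for neither baseline VAS nor pre-treatment expectations, although both are collected; the test stays valid but loses precision and leaves chance imbalance in expectations unadjusted.

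*Protocol article*

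**What the plan says.** All references are to the protocol article.

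- **Collected before treatment.** Design: "At baseline the participant will fill out the Visual Analogue Pain Rating Scale (VAS), the Neck Disability Index (NDI" and the EQ-5D-5L. Randomization: "each participant will be asked prior to the first treatment about their expectations regarding new and conventional treatments".
- **Purpose given for the expectation question.** Randomization introduces it with "To minimize any possible effects of expectations of treatment, each participant will be asked prior to the first treatment". Blinding adds that "the expectations of the patient regarding the new and conventional treatments are retrieved beforehand and taken into consideration during the evaluation of the data". The Discussion repeats this in the paragraph that opens "One of the trial’s weaknesses might be regarding blinding. We addressed this issue in different ways".
- **Primary outcome.** Patient-rated VAS before and after each of three treatments and at 6 weeks, 3 months and 6 months.
- **Primary analysis.** Statistical analyzes: if the data are normally distributed, changes in VAS go into a repeated-measures ANOVA that examines group by time. No covariate is listed.
- **Where expectations are used.** In the logistic model for improved versus not improved on the PGIC: "Independent variables will be age, sex, expectations, manipulation and duration of complaints".
- **How long unawareness lasts.** Blinding: "the therapist who is conducting the treatment will be kept unaware of the treatment method until the manipulation is applied". The manual technique is given supine. The device is used prone, and beforehand "the patient is instructed that they will hear a rattling sound that indicates the thrusts conducted by the device".

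**The concern.** Three sections offer the expectation question as a safeguard. Asking a question does not reduce the effect of the answer; only the analysis can use it, and the primary analysis as described does not. The primary outcome is self-rated pain, and patients can tell the two techniques apart once treated, so this is the outcome for which expectations matter most.

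Baseline VAS enters the ANOVA as a level of the time factor or through the change, not as a covariate. In a trial of 54 patients sized for 80% power with two spare patients per arm, the precision given up is worth having. A chance difference between arms in preference for the new device would stay unadjusted in the primary result.

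**Working it through.** **Inputs from the document (Number of test subjects).** Two-sided alpha 5% (z = 1.96), power 80% (z = 0.842), SD 15 mm, difference 12 mm, two extra patients per arm. The text does not say whether 15 mm is the SD of one VAS score or of a change.

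**Assumed, not in the document.** Baseline to follow-up correlation r = 0.3, 0.5, 0.7, and equal SDs at both times. Extra variance explained by expectations q = 0 to 10%.

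**1. The plan's own figure.** 2 × (1.96 + 0.842)² × 15² / 12² = 24.53, so 25 per arm; 25 + 2 = 27 per arm, 54 in total. It reproduces. Power from the noncentral t is 79.1% at 25 per arm and 82.2% at 27. The formula is an unadjusted two-group comparison without a correlation term.

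**2. Precision, if 15 mm is the SD of one score.** Change score: SD = 15√(2(1-r)). Baseline-adjusted: residual SD = 15√(1-r²). The variance ratio is (1-r²)/(2(1-r)) = (1+r)/2. Power is for one follow-up, 25 per arm, 12 mm.

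| r | SD change | Power | SD adjusted | Power | Variance ratio |
|---|---|---|---|---|---|
| 0.3 | 17.75 | 64.9% | 14.31 | 82.7% | 0.65 |
| 0.5 | 15.00 | 79.1% | 12.99 | 89.2% | 0.75 |
| 0.7 | 11.62 | 94.7% | 10.71 | 97.2% | 0.85 |

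**3. Precision, if 15 mm is the SD of change.** Unadjusted power is 79.1% whatever r is. The adjusted SD is 15√((1+r)/2) = 12.09, 12.99, 13.83 mm, giving 93.0%, 89.2%, 85.2%.

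**4. Adding expectations.** At r = 0.5 under the reading in step 2, residual SD = 15√(1 - 0.25 - q). For q = 0 this is 12.99 mm (89.2%); for q = 10% it is 15√0.65 = 12.09 mm (about 93%).

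**5. Cost in degrees of freedom.** Baseline VAS alone leaves 50 - 3 = 47. Three further covariate terms leave 44, and power falls by about 0.1 percentage point.

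**6. What a baseline imbalance does.** Let the arms differ by d at baseline. Given d, the expected follow-up difference is the treatment effect plus r·d. Subtracting d leaves the treatment effect minus (1-r)d in the change contrast. One standard error of d at 25 per arm is 15√(2/25) = 4.2 mm, which carries over as about -3.0, -2.1 and -1.3 mm at r = 0.3, 0.5, 0.7.

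**The case against.** **The Blinding text does not name the primary model.** It promises only that expectations will be considered when the data are evaluated, and the PGIC regression does that. This stands: a reader might infer that the plan breaks its own promise, but the promise is met for a secondary outcome. The gap is confined to the primary one.

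**An article may leave covariates to a fuller plan.** This stands only in part. The article names the primary model and lists the covariates of another model, placing expectations there. The point concerns what it states.

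**Baseline imbalance is already handled.** Largely right. A reader might infer that a baseline pain difference passes straight into the primary result. It does not: a constant difference falls in the group main effect, not in group by time, and only the -(1-r) share carries over. That share is random, not systematic, and the test's type I error already allows for it.

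**The power figures are not the plan's power.** Correct. The plan tests an interaction over nine VAS occasions (six around treatments, three at follow-up). The figures compare single-follow-up contrasts at assumed correlations. The 65% appears only if 15 mm is the SD of one score and r is 0.3.

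**A covariate does not cure unblinding.** Correct. Randomisation balances pre-treatment expectations on average. A main-effect term deals with chance imbalance only. A reader might infer that adjustment would protect against patients knowing their technique; it would not.

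**The blinding limit is disclosed.** Partly. The article claims therapist unawareness only up to the manipulation, seals questionnaires from the therapist, de-identifies data entry and calls blinding a possible weakness. It still lists expectations among the answers to that weakness without saying what their use can achieve.

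**Conclusion.** The point holds as an improvement in precision and balance for the primary model, not as an error that invalidates it. Among the analyses described, expectations reach only the PGIC regression, and baseline VAS is a covariate in none.

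For a single follow-up contrast, baseline adjustment gains about 18, 10 and 3 percentage points of power at r = 0.3, 0.5, 0.7 if 15 mm is the SD of one score, and about 14, 10 and 6 points if it is the SD of change. There is a gain under both readings at every r tried, but its size rests on assumed correlations and does not translate directly to the multi-occasion interaction test. The contribution of expectations cannot be sized from the document; the 0 to 10% range is illustrative.

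The documents do not support the claims that the ANOVA is biased by its lack of covariates or that adding expectations would repair the loss of blinding.

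**What to change.** **Statistical analyzes.** Analyse the post-baseline VAS values with a repeated-measures ANCOVA or a mixed model containing group, time and group by time. Enter baseline VAS as a covariate instead of as a level of time. Add pre-treatment expectations regarding the new and conventional treatments as a pre-specified covariate, and state how the answers are coded, since the article says only that patients are asked. Report the arm-by-expectation term as exploratory.

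**Randomization, Blinding and Discussion.** State which analyses use expectations. State that the adjustment addresses chance imbalance and precision and does not remove bias from patients and the therapist knowing the technique after the first manipulation.

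**Cost.** Both variables are already collected, so no new data are needed. The model has to be restructured, because baseline should not be both a time level and a covariate. A few degrees of freedom are spent, about 0.1 percentage point of power. Recruitment was ongoing when the article was written, so the change is best fixed before the data are analysed.
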